#### Secondary outcomes

These outcomes will be assessed at 6 and 12 months after randomization. Participants may also attend at other time points for clinical reasons. At the 6 month (+/- one month) and 12 month visits (+/- one month), a full clinical examination will be performed on those who return. Data on IOP and visual acuity will be recorded. Participants who do not attend the 6 and/or 12 month visits will be traced, initially by telephone, requesting them to visit. If they still do not attend the clinic, they will be visited in their home, where their visual acuity will be measured using a LogMAR chart, and IOPs measured using a Tonopen.

### Other measures

These will be assessed at 6 and 12 months after randomization. Adherence to topical medication in those not undergoing surgery or laser treatment will be assessed using the Morisky score
[14] (Additional file
5). This can be administered over the phone, if necessary. Prior to assessing reasons for not undergoing surgery or laser treatment, the following will be assessed after taking verbal consent: a) whether they did in fact attend for surgery at ABUTH, but slipped through the net; b) they underwent surgery or laser treatment in another hospital, or were given more eye drops elsewhere; and c) they have not had any treatment for their glaucoma apart from the eye drops given at the time of recruitment.

Those who have not had any further treatment will be interviewed to find out why they did not attend. This can be administered over the phone. A subset of those not attending will be selected randomly, and visited in their homes for in-depth interviews where they will be asked why they did not return to the hospital. Responses will be probed to better understand the barriers that led to non-acceptance of laser or surgery. See Additional file
6 for the interview guide and probe questions.

### Data collection

The following data will be collected using pre-tested data forms (Additional file
5).

### Before and after recruitment at T0

Data will be collected for name, age, gender, clinical findings and date given to attend for surgery or laser treatment. For those who refuse, reasons for not agreeing to participate will be sought. For those who agree, contact details will be recorded: detailed address; telephone numbers of individual/family/neighbor; sociodemographic data and randomization sequence number. All data will be entered into a customized, password protected database on the day of recruitment. The form will be kept in a lockable cupboard only accessible to the project manager in an office dedicated to the trial, which is locked when not in use.

For those allocated to MIG the interview will be conducted at T0. If a second MI session is indicated, the reason for this will be recorded. After every interview, WAI questionnaires will be completed independently by the participant and the interviewer. These forms will be kept in a lockable cupboard in a separate office dedicated to the MIG interviews. This office will be locked at all times when not in use for MIG sessions. The project manager and ophthalmologist will not have access to these forms at any time. Data from these forms will be entered into a separate password protected database.

### At time of ascertainment of primary outcome T1

Information on whether the participant underwent laser or surgery, which procedure was performed, and the date of the procedure will be recorded.

### At time of ascertainment of secondary outcomes T2 and T3

The date attended and the IOP and visual acuity in the study eye will be recorded. The Morisky Adherence questionnaire will be administered. At T2 only, the reasons for not undergoing surgery or laser will be sought using closed-ended questions. Consent will be obtained to record all in-depth interviews. (See Additional file
6 for interview guide for in-depth interviews.)

### Data management

#### Data entry

Databases have been created in Epidata and Access, with range and consistency checks. Data will be double entered by the project manager, who has been trained in data entry. Data will be entered as soon as possible after recruitment, so that the ‘surgery date’ and ‘tracing date’ outputs can be generated (as above). Random checks of the quality of data entry will be undertaken by [name] on a regular basis. Frequency distributions will be explored and data of outliers checked for accuracy.

### Data analyses

The randomization code will only be broken once analysis of the primary outcome is completed. We will prepare a flow chart describing participant flow through the trial. This diagram will provide data on the following: the number of eligible people approached to take part in the trial, the number of people who agreed to take part, reasons for non-participation, the number of people randomly allocated to MIG and no MIG, the number of people who received the intervention as randomized, the number of people with data on the primary outcome by the intervention group, and the number of people followed up at 6 and 12 months by the intervention group.

We will compare people who agreed to take part in the trial with people who did not agree to take part in terms of age, sex, education and stage of glaucoma to assess the generalizability of the findings. All participants will be analyzed in the group to which they were randomized (by intention to treat).

We will compare the characteristics of the people in the two intervention groups with respect to age, sex, education, distance from hospital and stage of glaucoma at presentation to assess the balance between intervention groups.

We will describe the quality of the MIG in two ways. Firstly, by the WAI questionnaire scores for participants’ and interviewers’ perceptions of the MIG sessions. We will analyze this as a continuous variable but it is likely that the data will be skewed and we will therefore present medians, ranges and interquartile ranges, by interviewer. We will also compare this to other published data on WAI scores. Secondly, by fidelity testing using the MITI scale, which generates a series of scores that can be categorized as good or poor. We will present results by interviewer as done in published studies using the MITI.

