**Methods:**

This is a hospital based, single centre, randomized controlled trial of MIG plus an information sheet on glaucoma and its treatment (the latter being “standard care”) compared with standard care alone for glaucoma patients where the treatment recommended is surgery or laser.

Those eligible for the trial are adults aged 17 years and above who live within 200 km of Bauchi with advanced glaucoma where the examining ophthalmologist recommends surgery or laser. After obtaining written informed consent, participants will be randomly allocated to MIG plus standard care, or standard care alone. Motivational interviewing will be delivered in Hausa or English by one of two MIG trained personnel. One hundred and fifty participants will be recruited to each arm. The primary outcome is the proportion of participants undergoing laser or surgery within two months of the date given to re attend for the procedure. MIG quality will be assessed using the validated MI treatment integrity scale.

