Everyone suspected of having glaucoma will be referred to the ophthalmologist (usually [name], but other ophthalmologists will also be trained to detect those who are eligible) for a detailed routine ophthalmic examination. The ophthalmologist will confirm the diagnosis of POAG and determine the treatment of choice based the clinical findings (severity) and socio-economic factors likely to influence adherence to medical treatment (such as education and distance from the hospital). Long-term eye drops will be recommended for those who live near the hospital, are educated and can afford topical medication. These individuals will not be eligible for recruitment. Surgery or laser treatment will be recommended for those with an advanced stage of the disease where this offers the best hope for preventing blindness. These individuals will be potential participants. The ophthalmologist will then explain the disease, the treatment options, and the purpose of treatment, as is standard of care. Participants will choose whether to have laser treatment or surgery. The ophthalmologist will then prescribe eye drops and explain how they are to be used whilst waiting for surgery or laser treatment. Everyone offered surgery or laser treatment will be given a date within one month to re-attend for the procedure. Their name and hospital registration number will be written in the surgical register. They will then be escorted to the project manager for recruitment. Participants wishing to change their date of treatment will be offered a new date, and the surgical register, data record form and spreadsheet will be updated.

The eligibility of each potential participant will be checked by the project manager. All those eligible will be recruited after obtaining written informed consent. If the patient does not consent, reasons will be sought and recorded. After obtaining consent a unique identifier number will be issued. All those recruited will be given a red ID card which contains their name, hospital number and study ID. They will be required to present this card at the registration desk at every visit.

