### Outcomes

#### Primary outcome

The primary outcome will be the proportion of participants undergoing laser treatment or surgery within two months of the date given to attend the hospital for the procedure (Table 
2. Participant timeline).

**Table 2 T2:** Participants time line

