### Blinding

Only participants allocated to MIG and the interviewers will know who has been allocated to MIG. The project manager and study ophthalmologist, who will be responsible for obtaining and checking data on the primary outcome, will be blinded to the intervention.

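### The code-break rule waits only for the primary analysis, so it permits unblinding while 6- and 12-month IOP and acuity data are still being collected

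*Protocol article*

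**What the plan says.** Under Data analyses, the protocol article gives one condition for breaking the code: "The randomization code will only be broken once analysis of the primary outcome is completed". It names no recipient of the code and sets no condition about later follow-up.

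The primary outcome closes early. Under Identification of potential participants and recruitment: "Everyone offered surgery or laser treatment will be given a date within one month to re-attend for the procedure". The outcome is then uptake "within two months of the date given to attend the hospital for the procedure".

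The secondary outcomes run much longer. Under Ascertainment of outcomes, Secondary outcomes: "These outcomes will be assessed at 6 and 12 months after randomization". The same section adds: "At the 6 month (+/- one month) and 12 month visits (+/- one month), a full clinical examination will be performed on those who return". For participants who stay away after a telephone request, the plan is this: "they will be visited in their home, where their visual acuity will be measured using a LogMAR chart, and IOPs measured using a Tonopen".

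The Blinding section first limits knowledge of the allocation to MIG participants and the interviewers. It then turns to the project manager and the study ophthalmologist, "who will be responsible for obtaining and checking data on the primary outcome, will be blinded to the intervention".

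**The concern.** The rule protects the primary outcome and is silent on what comes after it. Tonometry and chart acuity depend on the examiner, more so than an entry in a surgical register. Tracing effort and home visits also leave room for knowledge of the arm, or of the primary result, to influence who is measured and how. At 6 months from the date given, a subset of those who did not take up treatment is recontacted and offered it again (Other data section). Staff who know the arms could handle that contact differently, which could carry through to the 12-month IOP.

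This matters because IOP at 12 months is not incidental: the Sample size calculation section gives it its own power statement. There is also a practical route to unmasking. The participant form carries the randomization sequence number (Randomization section) and is held by the project manager, who enters the data. Once the list is released, that number is enough to identify the arm.

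**Working it through.** **Figures stated in the plan.** The article gives no figure for the follow-up outstanding at the code break. It does give power of 0.84 for a 5 mmHg difference in 12-month IOP with SD 14. That reproduces with 137 per arm (two-sided 5%): 5 / (14 × √(2/137)) − 1.96 = 2.956 − 1.96 = 0.996, and Φ(0.996) = 0.84. So 12-month IOP is meant as a powered comparison.

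**Inputs**
- Sample: "One hundred and fifty participants will be recruited to each arm", so 300 in total.
- Accrual: 70 recruited from the start of September 2013 to the end of January 2014 (Trial status), 70 / 5 = 14 a month; about 20 a month in the pilot (Findings of the pilot study). Recruitment would take 300 / 14 = 21.4 or 300 / 20 = 15 months.
- Primary outcome known: up to 1 month to the date given, plus 2 months, so 3 months after randomization. Taking the full month is cautious; a shorter wait would leave more visits outstanding.
- Visits v: 6 and 12 months. Window w: 0 or 1 month.
- Analysis time d after the last primary outcome is due: not stated, so varied from 0 to 9 months.

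**Earliest break against last measurement.** If the last participant is randomized at month L, primary data are due at L + 3 and the last 12-month visit at L + 12, or L + 13 with the window. The gap is 12 − 3 = 9 to 13 − 3 = 10 months.

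**Participants still awaiting a visit at the break.** With uniform accrual, the number outstanding is rate × max(0, v + w − 3 − d). The multiplier never exceeds 10 months, which is shorter than either recruitment period, so the cap of 300 is not reached.

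| Analysis time d | 12-month visit, no window | 12-month visit, +1 month | 6-month visit, no window | 6-month visit, +1 month |
|---|---|---|---|---|
| 0 months | 9 × 14 = 126 to 9 × 20 = 180 (42-60%) | 140 to 200 (47-67%) | 3 × 14 = 42 to 3 × 20 = 60 (14-20%) | 56 to 80 (19-27%) |
| 3 months | 6 × 14 = 84 to 6 × 20 = 120 (28-40%) | 98 to 140 (33-47%) | 0 | 14 to 20 (5-7%) |
| 6 months | 3 × 14 = 42 to 3 × 20 = 60 (14-20%) | 56 to 80 (19-27%) | 0 | 0 |
| 9 months | 0 | 14 to 20 (5-7%) | 0 | 0 |

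The exposure lies mainly in the 12-month visit. The 6-month visit is affected only if the analysis is quick. Attrition and revised procedure dates are ignored; a revised date for a late recruit would delay the earliest break and lower the counts.

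**The case against.** The strongest reply is that the sentence sets a not-before condition. It schedules no break and does not say that examiners or tracers will be told. A reader might infer that the plan removes blinding for IOP and acuity; the text does not go that far.

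A reader might also infer that the Blinding section covers the primary outcome only. That is not supported either. Its first sentence limits who knows the allocation without restriction by outcome or time, and the clause on primary data describes what the two staff members do. Other safeguards point the same way: the tracing spreadsheet omits the sequence number, the project manager and ophthalmologist never see the interview questionnaires, and identifiers are removed before analysis. The code-break sentence could well concern only the analyst's arm labels.

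It can further be said that MIG participants know they were interviewed and may say so at any visit, that real analysis takes time, and that an article may leave the naming of assessors and recipients of the code to the full protocol.

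Much of this stands. It limits the claim to what the rule permits, and it makes the zero-delay counts an upper case for each accrual rate and window. It does not answer the point that the one stated trigger ignores the 6- and 12-month data, and that no section keeps the code or arm-level results from the later assessors once it has been met. Imperfect masking is also no reason to add release of the code and the result.

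**Conclusion.** The point holds as a statement about timing. The rule allows the code to be broken 9 to 10 months before secondary follow-up ends, with 42-60% of 12-month visits and 14-20% of 6-month visits outstanding at the earliest moment, or 28-40% and about 0% after a 3-month analysis (no visit window in either case). These shares rest on uniform accrual at 14 to 20 a month, a procedure date one month after randomization, no attrition, and a primary analysis run once all 300 participants have reached their primary time point.

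The two visits should not be merged into one statement that up to half of participants are outstanding: at 12 months half is not the upper limit, and at 6 months the share is far lower. The primary comparison is not touched, because its analysis comes before any break. What is exposed is the credibility of IOP and acuity, including the powered 12-month IOP comparison.

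**What to change.** Change the sentence under Data analyses so that the primary analysis is run on coded arms, and neither the code nor arm-level results are released to anyone who measures, traces or enters data until the 12-month data are locked. Extend the Blinding section to name the 6- and 12-month IOP and acuity assessors and to state that they stay masked until that lock.

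With this rule, no secondary assessment is outstanding when site staff learn the arms. The change is one of wording and, with 70 of 300 recruited at the time of writing, can be made well before the present trigger could be met. The cost is that site staff wait about 9 to 10 months longer than the earliest date now allowed before they see the primary result. Disclosure by participants would remain possible.

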### Primary outcome

Our primary outcome is dichotomous (did or did not attend surgery or laser treatment within two months of their scheduled date). Our effect measure will be the risk ratio, that is, we will calculate the proportion of people with this outcome in the intervention group compared to the standard care group. We will report this with 95% confidence intervals. In a trial of 300 people we anticipate that the groups will be fairly well balanced. However, we will also calculate a risk ratio adjusted for factors that may affect uptake of surgery (stage of glaucoma, age, sex, education, and distance from hospital).

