### Sample size calculation

The sample size is based on the primary outcome and calculated using the SAMPSI command in Stata 12.1 statistical software (StataCorp Texas, USA). Based on the pilot study, we anticipate that 35% of participants in the standard care group will undergo surgery or laser within two months of the date given for the procedure. A sample size of 150 in each arm will be required to detect an acceptance rate of 52.5% (50% relative and 17.5% absolute increase in acceptance) in people in the intervention arm (power 0.8, alpha 0.05). This is based on a calculation of 137 in each arm rounded up to 150 in each arm to allow for loss to follow-up. We believe this absolute increase of 17.5% (corresponding to a relative increase of 50% assuming a 35% acceptance in the control group) would be an important effect to detect. We have also calculated the power of a study of this size to detect differences between the treatment groups with respect to the secondary outcomes. IOP at entry to the study will average approximately 35 mmHg (SD +/- 14 mmHg) (values resulting from the pilot study). Our outcome is based on the final IOP at 12 months. This is likely to be in the order of 25 mmHg in the standard care group. The study will have good power (0.84) to detect differences of 5mmHG or more between the two groups at one year.

We have less information on the probability of losing three or more lines of visual acuity over the year. Figure 
2 shows the proportion of participants losing three or more lines of visual acuity in the standard care group, with power curves for risk ratios of 0.5 and 0.8. It is more likely that we will be able to detect risk ratios in the order of 0.5. The power of the study to detect significant differences using a relative risk of 0.5 is shown in Table 
3.

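### Two risk ratios are planned for the primary outcome without saying which decides; letting the prespecified adjusted one lead would probably add a little precision at almost no cost

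*Protocol article*

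**What the plan says.** In the protocol article, Data analyses, Primary outcome, the main measure is simple: "Our effect measure will be the risk ratio, that is, we will calculate the proportion of people with this outcome in the intervention group compared" with standard care, reported with a 95% confidence interval. Two sentences then deal with baseline factors. The first is "In a trial of 300 people we anticipate that the groups will be fairly well balanced". The second is "However, we will also calculate a risk ratio adjusted for factors that may affect uptake of surgery", and the factors are "stage of glaucoma, age, sex, education, and distance from hospital".

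The opening part of Data analyses lists the same five factors for a descriptive comparison of the arms: "age, sex, education, distance from hospital and stage of glaucoma at presentation to assess the balance between intervention groups".

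The Sample size calculation is a plain comparison of two proportions: "we anticipate that 35% of participants in the standard care group will undergo surgery or laser within two months of the date given", against "52.5% (50% relative and 17.5% absolute increase in acceptance) in people in the intervention arm (power 0.8, alpha 0.05").

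The Subgroup analysis section refers to the primary outcome risk ratio as if there were only one. The Secondary outcomes analysis section says that dichotomous secondary outcomes are handled in the same way as the primary.

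**The concern.** The order of the sentences, the word 'also' and the unadjusted sizing together suggest that the crude ratio leads and the adjusted ratio is an extra. The only reasoning given around this choice is about balance. In a randomised trial, chance imbalance is the lesser reason to adjust. A baseline factor that predicts uptake explains part of the outcome variation, so adjusting for it narrows the interval for the same marginal risk ratio even when the arms are perfectly balanced. The protocol names five candidate predictors in advance and already plans to have them for both arms, yet the reading it invites leaves them out of the headline estimate.

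Two things are at stake. One is some precision on the primary outcome, in a trial whose Discussion concedes power of 0.69 if control uptake is 30%. The other is clarity: with two ratios for one outcome and no stated lead, a reader cannot tell in advance which one the conclusion will follow.

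**Working it through.** **Inputs from the protocol.** Control uptake 0.35, intervention uptake 0.525 (difference d = 0.175), power 0.80, alpha 0.05 (taken as two-sided; the protocol does not say), 137 per arm raised to 150, 1:1 allocation.

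**Assumption.** The strength with which the five factors jointly predict uptake is not given. It is expressed as R², the share of outcome variance explained, and a range is shown.

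**1. Reproduce the plan's figure.** With mean proportion 0.4375, the uncorrected size is

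n = [1.96·√(2·0.4375·0.5625) + 0.8416·√(0.35·0.65 + 0.525·0.475)]² / 0.175² = (1.3750 + 0.5812)² / 0.030625 ≈ 125.

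The continuity correction, n/4·[1 + √(1 + 4/(n·d))]², gives 137, which is the stated figure. Inverting the correction at 137 per arm gives power 0.803 for the design case. For the three Discussion scenarios it gives 0.686, 0.838 and 0.895, against the stated 0.69, 0.84 and 0.90. The sizing is therefore for the unadjusted comparison, and it is correct on those terms.

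**2. Approximate effect of adjustment.** Adjustment multiplies the variance by about (1 − R²), so the effective size is n/(1 − R²). With the same continuity-corrected power:

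| Assumed R² | 35% v 52.5%, 137 per arm | 35% v 52.5%, 150 per arm | 30% v 45%, 137 per arm |
|---|---|---|---|
| 0 | 0.803 | 0.840 | 0.686 |
| 0.02 | 0.811 | 0.848 | 0.696 |
| 0.05 | 0.824 | 0.859 | 0.711 |
| 0.10 | 0.846 | 0.879 | 0.736 |
| 0.20 | 0.888 | 0.915 | 0.790 |

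On the interval scale, the crude standard error of the log risk ratio at 150 per arm is √(0.65/52.5 + 0.475/78.75) = 0.1357. For an observed ratio of 1.5 the 95% CI is 1.15 to 1.96. At R² = 0.10 it becomes 1.17 to 1.93, and at 0.20 it becomes 1.18 to 1.90.

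**3. Check by simulation.** 4,000 trials per setting, 150 per arm, 35% v 52.5%. The crude log risk ratio was compared with a marginal risk ratio standardised from a logistic model with arm and five covariates. There is no continuity correction here, so crude power is near the uncorrected 0.867.

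| Strength of the five factors | Power, crude | Power, adjusted | Standard error ratio, adjusted/crude |
|---|---|---|---|
| R² 0 | 0.857 | 0.855 | 1.008 |
| R² 0.012 | 0.864 | 0.862 | 0.998 |
| R² 0.045 | 0.860 | 0.868 | 0.986 |
| R² 0.092 | 0.864 | 0.886 | 0.961 |
| R² 0.145 | 0.865 | 0.909 | 0.932 |

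A separate simulation, indexed by the joint AUC of the factors, gave 0.86 v 0.88 (AUC 0.65), 0.87 v 0.91 (0.71) and 0.87 v 0.93 (0.76). Its standard error ratios were 0.971, 0.938 and 0.901, which imply R² = 1 − ratio² of about 0.06, 0.12 and 0.19. The equivalent number of extra participants is 300·(1/ratio² − 1) = 18, 41 and 70. With 35% uptake in both arms, the type I error of the adjusted analysis was 0.045 to 0.052.

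**4. Can the data carry the model?** Expected events at 150 per arm are 52.5 + 78.75 ≈ 131. With one term per factor the model has seven parameters: intercept, arm and five covariates.

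**The case against.** The strongest reply is that nothing here is wrong. An unadjusted intention-to-treat risk ratio is valid in a 1:1 randomised trial, and it matches the sizing exactly. The adjusted ratio is prespecified, unconditional and has fixed covariates, so it will be reported in any case. Its estimator and coding can properly sit in an analysis plan that is not shown. All of this stands, and it limits the point to efficiency and labelling.

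The reply on size also largely stands. The protocol says only that the factors may matter. Recruitment is restricted to advanced disease and to residence within 200 km. Educated patients living near the hospital who can afford drops are not recruited. Narrowing stage, distance and education in this way probably weakens them as predictors. At 30% control uptake, even R² = 0.20 leaves power at 0.79.

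Some stronger readings are tempting but not supported:

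- *The conclusion rests on the crude ratio.* This is an inference from word order and sizing; the protocol does not state it.
- *The adjusted ratio is justified by balance.* Balance is offered in support of the crude ratio. The adjusted one follows as a contrast, and the reason given for it is that the factors may influence uptake.
- *The false-positive rate is inflated.* If either ratio could count as the result, simulated type I error is 0.062 to 0.066. The protocol does not say that either may count, and if the crude ratio decides, this inflation does not arise.
- *Power is being given away.* That holds only if the factors predict uptake, which the documents do not show.
- *All five factors are recorded before randomisation.* The data collection section covers the time before and after recruitment at T0 and does not fix that order for every item.

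What the reply does not remove is that the article fixes the order of the two ratios and the reasoning around them, leaves out precision, and does not name the deciding result.

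**Conclusion.** The point holds as a modest one. The crude ratio is sound and consistent with the sample size; the protocol misses an inexpensive gain and leaves the deciding ratio unnamed. At the design rates and 150 per arm, letting the adjusted marginal ratio lead changes power by about nothing if the factors barely predict uptake, and adds roughly 1 to 6 percentage points if they predict weakly to moderately. The lower part of that range is more plausible given who is recruited. The trade is lopsided: the simulated loss with useless covariates was 0.2 points, within simulation error. The size rests on assumed covariate strength, a two-sided 5% test, complete baseline data and the design uptake rates. It does not alter the sample size or suggest bias.

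**What to change.** In Data analyses, Primary outcome, name one deciding result: the marginal risk ratio with 95% CI, standardised from a logistic model containing arm and the five factors already listed. This targets the same quantity as the crude ratio, so the hypothesis and the meaning of the sample size are unchanged. Report the crude ratio as supportive. Replace the sentence on expected balance with a statement that adjustment is for precision and that the conclusion follows the adjusted ratio whatever the baseline comparison shows. If the investigators prefer to keep the crude ratio in the lead, they should say that it decides; this settles the labelling but not the precision.

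The cost is a change of analysis wording. Recruitment has begun, but the randomisation code stays unbroken until the primary analysis is finished, so the amendment can still be made blind and reported as the Protocol amendments section provides. The drawbacks are a slightly less transparent calculation and the need for complete baseline data on the five factors, which the planned comparison of the arms already requires.
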